## Accountability and Disposal

The study pharmacists are required to maintain complete records of all study products received from the Sponsor and/or drug manufacturer and will be responsible for maintaining an accurate record of the randomization codes, inventory, and an accountability record of amoxicillin DT and placebo supplies for this study. The study pharmacists will also be responsible for ensuring the security of these documents, maintaining them under lock and key and/or electronic encryption. Partially used amoxicillin DT and placebo will not be used for human administration.

At the completion of the study, the study pharmacists and site investigators (or designee) will conduct and document a final reconciliation of all study product shipped, received, dispensed, consumed, and remaining. Any discrepancies identified will be investigated, resolved, and documented before any unused study drug is destroyed. After all accounting and reconciliation procedures are complete and approved by the Sponsor, all unused study product will be destroyed on site and documented in the master study files.

## DATA COLLECTION

Clinical research data will be maintained through a combination of secure electronic data management system and physical files with restricted access. Data related to study endpoints will be extracted from the electronic databases for statistical analysis. Three distinct study databases will be created and maintained: the primary study database with study visit data, a safety database with SAE assessments, and a database with participating children’s personally identifiable information.The first two study databases containing study endpoint data will identify children only by study identification numbers and will not contain identifying information such as name, address, medical record number or personal contact information. In the third database, the study coordinator will maintain a log that will contain the link between personal identifiers and the study participant IDs. The linklog and any other documentation (paper-based or electronic) that has both personal identifiers and the participant ID will have restricted access and will be stored in a secure manner separately from other study data and will be retained for at least five years after the last participating child exits the study.

## Case Report Forms

All study data will be collected by the clinical study staff using designated source documents or paper-based case report forms (CRFs). Study data will be entered directly into the CRFs during a study visit. Data from the paper-based CRFs will be entered after the fact into the electronic database as promptly as is feasible. Study staff will maintain source documents for each child at the study site. Source documentation will be available for review to ensure that the collected data are consistent with the CRFs. CRFs and laboratory reports will be reviewed by the site clinical team who are responsible for ensuring that they are accurate and complete. CRFs, source documents and other supporting documents (both electronic and paper-based) will be kept in a secure location and remain separate from participant identification information (name, address, etc.) to ensure confidentiality. Standard Good Clinical Practices (GCP) practices will be followed to ensure accurate, reliable and consistent data collection.

## Source Documents

Source documents include but are not limited to:

- Signed informed consent forms
- Documentation of the comprehension checklist
- Visit documentation that includes dates of study visits
- Receipts for travel reimbursement
- Reported laboratory results
- Clinic notes

A copy of all laboratory results will also be included in the child’s medical records. Site investigators will maintain, and store in a secure manner, all source documents throughout the study. These documents will be retained for at least five years after the last child exits the study.

## DATA MANAGEMENT

Primary data management activities will be undertaken by the designated contract research organization (CRO). The on-site study data manager will oversee data-related procedures at the study site and will be supervised by the CRO data management staff. Data management activities include data entry and validation, data coding and cleaning, database quality control, disaster recovery plans, adverse event reporting and tracking systems, preparation and submission of safety and compliance reports to the sponsor, and preparation of final study database. Data management activities will be performed using Clindex® Clinical Trial and Data Management software, developed by Fortress Medical Systems.

## Data Access

The participating site will maintain appropriate medical and research records for this trial, in compliance with International Conference on Harmonization Good Clinical Practice E6 (ICH-GCP), regulatory, sponsoring organization and institutional requirements for the protection of confidentiality of children.The site will permit authorized representatives of the sponsor and regulatory agencies to examine (and when required by applicable law, to copy) clinical records for the purposes of quality assurance reviews, audits and evaluation of the study safety and progress. User-specific usernames and passwords are required to log onto the database. User rights will be provided to study staff, PIs, and co-investigators at the level appropriate for each individual’s job description.

## Data Storage

The site investigators and designees will maintain, and store securely, complete, accurate and current study records throughout the study. In accordance with regulations, study staff will retain all study records on site for at least five years after study closure. Study records will not be destroyed prior to receiving approval for record destruction from the sponsor. Applicable records include source documents, site registration documents and reports, informed consent forms, and notations of all contacts with the child.

The Clindex® database is hosted by Fortress Medical Systems through their Software as a Service platform and accessed remotely online. All of the servers that host the Clindex® software and data are housed at ATOMICdata, a Tier 3, SOC 3 Certified Data Center. The primary hosting facility is at the ATOMICdata Minneapolis South facility.

## External Study Monitoring

The Study Sponsor and other regulatory authority inspectors or their authorized representatives are responsible for contacting and visiting the study site for the purpose of inspecting the facilities and, upon request, inspecting the various records of the trial. Participant confidentiality will be respected. Site monitoring visits will be conducted to assess compliance with ICH-GCP guidelines. Study monitors will visit the site to:

- Verify compliance with human subjects and other research regulations and guidelines
- Assess adherence to the study protocol and study-specific procedures manual
- Confirm the quality and accuracy of information collected at the study site and entered into the study database
- Assess the resolution of any past or ongoing issues identified at previous monitoring visits

The site investigators will allow study monitors to inspect study facilities and documentation (e.g., informed consent forms, clinic and laboratory records, other source documents, case report forms), as well as observe the performance of study procedures. Medical records containing identifying information may be made available for review when the study is monitored by the sponsor or an authorized regulatory agency. Direct access may include examining, analyzing, verifying, and reproducing any records and reports that are important to the evaluation of the study. Site visit logs will be maintained at the study site to document all visits.

## SAFETY ASSESSMENTS AND REPORTING

## Safety Monitoring

This protocol has extensive safety monitoring in place. The study site investigators will be responsible for close safety monitoring of all children participating in the study, and for alerting the protocol team if unexpected concerns arise. Children with chest-indrawing pneumonia will be hospitalized for the first two days to ensure initial continuous monitoring by hospital staff. Each participating child will be evaluated by a study clinician at each study visit. If a child misses a study visit, home visits will be conducted by trained study staff to ensure clinical evaluation. Every effort will be made to trace all children in the study for the final outcome assessment. An emergency number will be provided to all participants’ caregivers so that an on-call clinician can be reached at any time during study participation. As needed, children in the study may be evaluated at interim visits and/or referred for additional care. SAEs will also be regularly reviewed by the study’s CRO safety monitor and medical expert and compiled into reports for the protocol team. The protocol team may seek independent expert medical opinion as the need arises. In addition, an external group, the Data Safety and Monitoring Board (DSMB) will be closely involved in regular safety monitoring.

## Data Safety and Monitoring Board (DSMB)

An independent DSMB will be set up to regularly (approximately every 6 months) review cumulative safety and study conduct data. At a minimum, safety data presented to the DSMB will include summaries of data on AEs, SAEs, adherence rates, treatment failure, and clinical relapse. The DSMB will include at least one pediatrician, one pneumonia expert, and one biostatistician. As the interim analyses are available, the DSMB will review interim comparisons of the trial arms after enrollment has begun. The content, format and frequency of safety data reports will be agreed upon by the protocol team and the DSMB in advance of study implementation, to be documented in a DSMB charter. The DSMB may review the unblinded treatment regimens of individuals, if warranted. The DSMB reviews will be summarized with recommendations to the study Sponsor, as to whether or not there are safety concerns and if the study should continue without change, be modified, or terminated.

In the unlikely event that the protocol team has serious safety concerns that lead to a decision to discontinue study product allocation for all children in the study and stop accrual into the study, the protocol team will request an emergency review of the data by the DSMB before recommending that the study be permanently stopped. At the protocol team’s request, accrual into the study may be temporarily halted before the DSMB has the opportunity to review the relevant data by treatment arm.

## Adverse Events

Per ICH GCP guidelines, an adverse event (AE) is “any untoward medical occurrence in a patient or clinical investigation subject administered a pharmaceutical product and which does not necessarily have a causal relationship with this treatment. An adverse event (AE) can therefore be any unfavorable and unintended sign (including an abnormal laboratory finding), symptom, or disease temporally associated with the use of a medicinal product, whether or not related to the medicinal product.” These come to the attention of site clinicians through interim medical histories, physical examinations and laboratory testing. Study participants’ caregivers will be instructed to contact the study site staff to report any AEs they may experience. In the case of a life-threatening event, they will be instructed to seek immediate emergency care. Where feasible and medically appropriate, participant caregivers will be encouraged to seek medical care for their children where the study clinician is based, and to request that the clinician be contacted upon their arrival.

All AEs will be managed by the clinical study site team in accordance with good medical practices and the standard clinical practices in place at the hospital. The clinical team will assess and treat or refer the participating child for medical care as appropriate, which may include additional study visits, if necessary. If any acute treatment or medical care is required as a result of harm caused by a study product or study procedure, this care will be provided by the site free of charge. All children in the study with an AE will be followed clinically until the AE resolves (returns to baseline) or stabilizes.

## Serious Adverse Event

Serious adverse events (SAEs) will be defined per US 21Code of Federal Regulations (CFR) 312.32 guidelines, or the equivalent Malawi regulations, as AEs occurring that:

- - Result in death
  - Are life-threatening adverse events
  - Require inpatient hospitalization or prolongation of existing hospitalization
  - Result in persistent or significant disability/incapacity, or
  - Are congenital anomalies/birth defects.

Important medical events that may not result in death, be life-threatening, or require hospitalization may be considered serious when, based upon appropriate medical judgment, they may jeopardize the health of the participating child or require medical or surgical intervention to prevent one of the outcomes listed above.

Note that the initial hospitalization for children in ITIP2 does not count as an SAE as the condition for which the child was hospitalized occurred prior to administration of the study product, classifying it as a pre-existing condition and not an AE. If that initial hospitalization is prolonged past the expected duration of 2 days, because the child’s health has deteriorated or the child has not responded to the treatment and still needs hospital supervision, it will be reported as an SAE. Any readmission to the hospital will also be reported as an SAE. Please refer to Section 4.6 on Study Procedures, specifically the portion titled “Management of Study Participants During Hospitalization,” for further detail on discharge assessments and prolonged hospitalization.

All treatment failures will be considered SAEs.

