## Study Objectives

The broad objective of this study is to provide scientific evidence assessing the optimal duration of treatment with amoxicillin DT for chest-indrawing childhood pneumonia in the malaria-endemic setting in Malawi, Africa.

- - Primary Objective
    - To determine whether 3 days of treatment with oral amoxicillin DT in HIV-negative children 2 to 59 months of age with chest-indrawing pneumonia is as effective as 5 days of treatment.
  - Secondary Objectives
    - To determine whether the intervention arm has equivalent rates of treatment relapse as the control arm among those without treatment failure before or on day 6.
    - To determine whether the intervention arm has equivalent rates of combined treatment failure and relapse before or on day 14 as the control arm.
    - To determine whether the intervention arm has equivalent rates of adverse events (AEs) and serious adverse events (SAEs) as the control arm.
    - To investigate whether there may be a differential treatment response in children who test positive for malaria at baseline. This information will be useful to plan further childhood pneumonia and malaria integrated interventions in similar settings.
    - To determine whether there is a differential treatment response in enrolled children with wheeze during screening (identified prior to any bronchodilator administration).
    - To determine whether there is a differential treatment response in enrolled children with an oxygen saturation level <93% by pulse oximetry at baseline.
    - To determine whether there is a differential treatment response in enrolled children with mid-upper arm circumference (MUAC)-defined moderate malnutrition at baseline (11.5-13.5cm).
    - To determine whether there is a differential treatment response in enrolled children with very fast-breathing for age at baseline (>70 breaths per minute for 2–11 months, >60 breaths per minute for 12–59 months).
    - To determine whether there is a differential treatment response by age.

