## Therapy for Treatment Failure and Clinical Relapse

If a child is determined to have treatment failure on or before Day 6 or clinical relapse between Day 6 and Day 14, he or she will be hospitalized and will receive second-line therapy. At KCH, standard of care for children failing oral amoxicillin is to receive benzyl penicillin and gentamycin. Enrolled children failing treatment or experiencing clinical relapse will receive this regimen as inpatients, regardless of their randomization allocation.

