2. Proportion of children with either treatment failure or clinical relapse before or on day 14 (among all randomized children).
3. Proportion of children with AEs and SAEs.
4. Proportion of children with treatment failure among those testing positive for malaria by rapid diagnostic testing (mRDT) at baseline (overall).
5. Proportion of enrolled children failing treatment among those with wheeze during screening (identified prior to administration of bronchodilators).
6. Proportion of enrolled children failing treatment among those with oxygen saturation <93% by pulse oximetry at baseline.
7. Proportion of children failing treatment among those with MUAC-defined moderate malnutrition (11.5-13.5cm).
8. Proportion of children failing treatment among those with very fast-breathing for age (>70 breaths per minute for 2–11 months, >60 breaths per minute for 12–59 months).
9. Proportion of children failing treatment by age at baseline.
10. **STATISTICAL METHODOLOGY**

*7.1 Design*

The study will include 2,000 children aged 2 to 59 months. Children will be randomized to receive oral amoxicillin for 5 days (control) or 3 days + 2 days placebo (treatment). Treatment will be block randomized (with concealed block size) to ensure a 1:1 ratio of intervention and control. Randomization will be stratified by age group (2 up to 12 months, 12 up to 3 years, 3 years up to 5 years) and site (Bwaila District Hospital and Kamuzu Central Hospital).

*7.2 Interim analysis* We planned two interim analyses after about one-third and two-thirds of children have been enrolled. The seqDesign[2] software was used to determine the appropriate non-inferiority and futility stopping boundaries at each analysis. We assumed a one-sided test with an alpha=0.025, sample size = 1900 (assuming 5% loss to follow-up in each of the arms), a Pocock design for early inferiority and O’Brien-Fleming for early non-inferiority stopping boundaries and a 1.5 relative non-inferiority boundary.

The maximum true failure rates at both the interim analyses and final analysis for the 3-day group for which the 95% CI excludes the non-inferiority margin for various 5-day treatment group failure rates are provided in Table 1 below.

Table 1. Maximum true failure rates for the 3-day treatment arm beyond which stopping for early non-inferiority will be considered

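### Treatment failures and relapses are SAEs by rule, so the SAE part of the safety endpoint mostly repeats the failure-or-relapse result and is insensitive to other harms

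*Combined protocol and SAP*

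**What the plan says.** Three rules in the protocol act together.

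- Section 4.10, Serious Adverse Event: "All treatment failures will be considered SAEs". No exception is given.
- Section 4.6, Therapy for Treatment Failure and Clinical Relapse: a child with failure by Day 6, or with relapse after it, is admitted ("he or she will be hospitalized and will receive second-line therapy").
- Section 4.10 again: "Any readmission to the hospital will also be reported as an SAE". A prolonged first admission also counts when "the child has not responded to the treatment and still needs hospital supervision, it will be reported as an SAE".

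Failures are therefore SAEs directly, and relapses are SAEs through the readmission rule.

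The safety objective in protocol section 3 is "To determine whether the intervention arm has equivalent rates of adverse events (AEs) and serious adverse events (SAEs) as the control arm". The matching endpoint, in protocol section 3 and SAP 6.2 item 3, is "Proportion of children with AEs and SAEs". SAP 6.2 item 2 is a separate efficacy endpoint: failure or relapse by Day 14 among all randomised children.

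The SAP gives no method, model or margin for the AE/SAE comparison, and its Appendix A has no AE/SAE table.

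**The concern.** Under these rules the proportion of children with an SAE equals SAP 6.2 item 2 plus whatever other serious events occur. It includes children who count as failures only because of fever at Day 6, repeated vomiting of doses, or an antibiotic prescribed for a co-infection.

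The classification is reasonable for expedited reporting. As a comparison between arms it has two weaknesses. A difference in serious harms unrelated to efficacy is diluted by a large built-in component. Any difference in efficacy also reappears as a difference in SAEs, although it carries no new information.

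This matters because the protocol offers fewer antibiotic side effects as one reason for a shorter course (section 1), and names medication side effects as the risk in the 5-day arm (section 6, Risks to Participants). The SAE comparison as defined is poorly placed to show that trade-off.

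**Working it through.** **Inputs from the documents.** Control failure rate 8% (section 5.1); 1,000 children per arm and 5% loss, leaving 950 per arm (section 4.5); non-inferiority margin 4.0 percentage points at 8% failure (section 4.5).

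**Inputs assumed.** Relapse among non-failures, *r* = 0–5%. Other SAEs among the remaining children, *o* = 0.5–2%. Neither is in the documents.

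**The plan's own figure.** The plan states no figure for the SAE endpoint. The 8% rate underlies its 88% power for the primary test, which can be checked:

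SE = √(2 × 0.08 × 0.92 / 950) = 0.01245; power = Φ(0.04/0.01245 − 1.96) = Φ(1.25) = 89.5%.

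Simulating the stopping boundaries in SAP Tables 1 and 2 gives 86.8%. Both are within two points of 88%, so the inputs are consistent with the plan.

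**SAEs by definition.** 0.08 × 1,000 = 80 children per arm, or 160 of 2,000, before any relapse.

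**Make-up of the SAE proportion.** With *f* = failure rate:

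SAE = *f* + (1 − *f*)*r* + (1 − *f*)(1 − *r*)*o*.

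Example with *r* = 2%, *o* = 1%: failure plus relapse = 0.08 + 0.92 × 0.02 = 0.0984; SAE = 0.0984 + 0.9016 × 0.01 = 0.1074; share = 0.0984/0.1074 = 91.6%.

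**Power to see *o* double in one arm** (two-sided 5%, 1,000 per arm):

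power = Φ(|p₁ − p₂| / √{[p₁(1 − p₁) + p₂(1 − p₂)]/1,000} − 1.96).

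Same example, all SAEs: 0.1074 vs 0.1164, difference 0.0090, SE 0.0141, so Φ(0.64 − 1.96) = 9.3%. Other SAEs alone, 1% vs 2%: difference 0.0100, SE 0.0054, so Φ(1.84 − 1.96) = 45%.

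| *r* | *o* | SAE proportion | Failure share | Failure + relapse share | Power, all SAEs | Power, other SAEs alone |
|---|---|---|---|---|---|---|
| 0 | 0.5% | 8.5% | 94.6% | 94.6% | 5.5% | 25% |
| 0 | 1% | 8.9% | 89.7% | 89.7% | 10.5% | 45% |
| 0 | 2% | 9.8% | 81.3% | 81.3% | 26.4% | 75% |
| 2% | 0.5% | 10.3% | 77.7% | 95.6% | 5.1% | 25% |
| 2% | 1% | 10.7% | 74.5% | 91.6% | 9.3% | 45% |
| 2% | 2% | 11.6% | 68.7% | 84.5% | 22.9% | 75% |
| 5% | 0.5% | 13.0% | 61.4% | 96.6% | 4.7% | 25% |
| 5% | 1% | 13.5% | 59.4% | 93.5% | 8.1% | 45% |
| 5% | 2% | 14.3% | 55.8% | 87.8% | 19.2% | 75% |

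The last column counts other SAEs at *o* and 2*o* among all 1,000 children per arm.

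**Confounding with efficacy** (*r* = 0).

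- Opposite effects can cancel. With failures of 8% (5-day) and 9% (3-day) and other SAEs of 2% and 1%, the SAE proportions are 0.08 + 0.92 × 0.02 = 9.8% and 0.09 + 0.91 × 0.01 = 9.9%.
- An efficacy loss alone can look like a safety signal. With failures of 8% vs 12% and other SAEs of 1% in both arms, the proportions are 8.9% and 12.9%, detected with about 81% power.

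**The case against.** A reader might infer that the endpoint cannot show a safety difference at all. The documents do not support that.

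- The endpoint also covers non-serious AEs. The common amoxicillin side effects listed in protocol section 2 are mostly of that kind, and dilution there is modest. For assumed non-failure AE rates of 20% vs 25%, power is 76% alone and 62% once 8% failures are added; for 10% vs 15% it is 92% and 74%.
- Relatedness is judged blind, with final determination by a medical officer for all SAEs and by an independent one for deaths. It is reported for AEs of grade 2 and above and for all SAEs (section 4.10).
- The DSMB receives AEs, SAEs, failure and relapse as separate items.
- Even within all SAEs, power to see a doubling is low rather than nil, and it depends on the assumed baseline. With no relapse it is 47% from a 3% baseline and 82% from 5%.

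A reader might also infer that the SAP prescribes a merged analysis, or that similar SAE rates will be presented as independent support for 3 days. The SAP is silent on method, and the documents make no such plan. Both arms take identical active drug on Days 1–3, so drug-related excess could come only from Days 4–5. The doubling is an illustration, not an expectation.

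It would also be wrong to make the line without efficacy events the headline. Protocol section 6 names more failures, further admissions and death as risks of the shorter course, and danger signs and hypoxia are real harms of under-treatment. Repeated vomiting of doses is a failure criterion, while vomiting is a listed drug side effect, so excluding failures could hide it.

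All of this stands. What remains is that the separation is not prespecified. The DSMB summaries serve monitoring rather than the reported comparison, and no analysis by relatedness is planned.

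**Conclusion.** The concern holds in a limited form. The SAE part of the endpoint largely repeats failure or relapse by Day 14, so it is insensitive to other serious harms and confounded with efficacy. The figure of about 80 children per arm follows from the plan's own 8% and 1,000. The 81–97% share, and the contrast of 5–26% with 25–75% power, rest on the assumed ranges for relapse and other SAEs. One secondary objective is affected. The primary analysis and the stopping boundaries, which use failure rates, are not. The objective of equivalent AE and SAE rates also has no margin, so equivalence could not be concluded from this comparison however the SAEs are counted.

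**What to change.** Leave SAE reporting and clinical management unchanged. In SAP 6.2 item 3, and in an AE/SAE table added to Appendix A, prespecify by arm and side by side:

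- (a) all AEs and all SAEs;
- (b) SAEs split by a blinded flag into those that are solely the treatment failure, the relapse or the admission for it, and all others;
- (c) product-related AEs and SAEs, with repeated vomiting of doses kept visible (Appendix A Table 2 has no row for it among the failure reasons);
- (d) all deaths.

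State that the all-SAE comparison is not independent of the efficacy result. Either give a margin for equivalent rates or call the comparison descriptive.

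The cost is SAP wording and one blinded yes/no per SAE, which can be added to the medical officer's existing review. It should be settled before unblinding, since a later split would be post hoc.
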